### Treatment protocol

After being admitted to the hospital, all patients will be assessed and receive standard treatment (including surgery, if necessary) in the neurology ICU in accordance with the current guidelines [25]. Those who meet the criteria and whose representative has signed an informed consent form will be enrolled in the trial and be randomly assigned to the stimulation or non-stimulation group according to the procedure mentioned above.

The patients in the stimulation group will receive RMNS in addition to standard treatment. The electrical treatment will be delivered via a pair of lubricated 1-inch square rubber surface electrodes pasted 1 inch apart on the volar aspect of the right distal forearm over the median nerve. An electrical neuromuscular stimulator (Verity Medical Ltd., Braishfield, UK) will supply trains of asymmetric biphasic pluses at an amplitude of 15–20 mA (as tolerated) with a pulse width of 300 μs at 40 Hz ON for 20 s and OFF for 40 s, which has been proven to be well tolerated without causing pain or skin irritation. The electrical stimulation treatment will last for 8 h per day for 2 weeks. Patients assigned to the control group will continue to receive the previous standard treatment without electrical stimulation. During treatment, all patients will receive intensive care to prevent hypotension, hypoxia, intracranial hypertension and disturbance of homeostasis.

In addition to vital signs and general data, some additional data from the case report forms (CRFs) will be assessed at the beginning of the trial and during treatment. Once enrolled in the trial, the GCS, Glasgow Coma Scale Motor Part (GMS), Full Outline of Unresponsiveness (FOUR) scale, Coma Recovery Scale-Revised (CRS-R) and Disability Rating Scale (DRS) scores of each patient will be collected.

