#### Statistical analysis

Analysis will be performed in accordance with the intention-to-treat principle. All randomised patients will be included in their original assigned group regardless of the actual treatment approach they receive. Categorical variables will be described as numbers and percentages and analysed by the chi-squared test. Normally distributed continuous variables will be presented as mean and standard deviation (SD) and compared using Student’s *t* test; non-normally distributed variables will be expressed as median and interquartile ranges and analysed using the Mann–Whitney U test. A two-sided significance level of 0.05 will be used.

Baseline data such as age and GCS score at admission will be tested for any imbalance. If imbalances are detected, those factors will be corrected using a multiple logistic regression model.

The primary endpoint, namely the percentage of patients regaining consciousness 6 months after injury, will be presented as total percentage per group and analysed as categorical variables. The secondary outcome variables describing clinical status throughout the treatment and follow-up will be analysed as continuous variables.

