This trial has some novel features compared with other major RMNS trials. First, it is an Asian multicentre randomised controlled trial. The previous trials only focused on one region or even a single hospital. This trial is the first to widen the scope to a whole continent, reducing selection bias to a great extent. Second, in this trial, the RMNS therapy starts at an early stage, 7–14 days after the injury. Research shows that the later the application of electrical stimulation, the longer the duration needed to obtain a similar outcome [14]. Earlier commencement of neuroresuscitation treatment can show more efficacy, as long as the patient is stable. Third, the ACES trial uses various kinds of assessment scales to evaluate the condition of participants. The assessments fall into two groups: recovery pace parameters and long-term outcome parameters. The former group includes the GCS, GMS and FOUR. The GCS includes eye opening, verbal and motor responses. It has been used ubiquitously in acute care databases and in studies of acute neurologic injury. However, the GCS has been deficient in measuring key components of neurologic examination used for prognostication and most conspicuously lacks assessment of the brainstem reflexes. The FOUR score has been developed to overcome these inadequacies. It consists of four components that evaluate eye responses, motor responses, brainstem reflexes and respiration patterns. Because of its greater neurologic detail, the FOUR score is of more benefit than the GCS in predicting mortality in the ICU. A recent large multicentre prospective study in critically ill patients found an excellent inter-rater agreement between paired clinicians [36–38]. The long-term outcome parameters are the CRS-R, DRS and GOSE. The CRS-R is a standardised neurobehavioural assessment tool comprising six hierarchically organised subscales (auditory, visual, motor, oromotor–verbal, communication and arousal). Scores range from 0 to 23, with higher scores indicating a higher level of neurobehavioural function [1]. The DRS, a measure of functional outcome, includes measures of eye opening, verbalisation and motor response; cognitive understanding of feeding, dressing and grooming; degree of assistance and supervision required; and employability. Scores range from 0 to 29, with higher values indicating greater disability [1, 39]. The GOSE has eight ordered categories: death, vegetative state, lower severe disability, upper severe disability, lower moderate disability, upper moderate disability, lower good recovery and upper good recovery. It was developed as an extended version of the GOS in response to the perceived lack of sensitivity of the latter. It is now the primary outcome measure in trials of TBI [40]. Using all these scales, we hope to evaluate the condition of the coma patients as thoroughly as possible.

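### Five secondary scales are compared without using their enrolment scores, and the ordinal GOSE is classed as continuous

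*Protocol article*

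**What the plan says.** The Study endpoint section lists six scales as secondary endpoints. GOSE, CRS-R and DRS are taken at 28 days, 3 months and 6 months after injury. GCS, GMS and FOUR are taken at those times and on days 1 and 7 after enrolment.

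The Statistical analysis section fixes how they are handled: "The secondary outcome variables describing clinical status throughout the treatment and follow-up will be analysed as continuous variables". Two routes are given for continuous variables. On the first, "Normally distributed continuous variables will be presented as mean and standard deviation (SD) and compared using" Student's t test. On the second, "non-normally distributed variables will be expressed as median and interquartile ranges and analysed using the Mann–Whitney U test". No covariate appears in either.

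The same section uses baseline data in one way only. First, "Baseline data such as age and GCS score at admission will be tested for any imbalance". Then, "If imbalances are detected, those factors will be corrected using a multiple logistic regression model".

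The Treatment protocol section lists GCS, GMS and FOUR among the scores taken once a patient is enrolled, and continues: "Coma Recovery Scale-Revised (CRS-R) and Disability Rating Scale (DRS) scores of each patient will be collected". The Data collection and follow-up section gives the same enrolment list without GMS. GOSE is in neither list. On GOSE itself, the Discussion says: "The GOSE has eight ordered categories: death, vegetative state, lower severe disability", and goes on up to upper good recovery.

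**The concern.** Two choices are stated in the text, not merely left open.

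First, five of the six scales have an enrolment value that is probably the best single predictor of the later value on the same scale, and the stated tests do not use it. The one adjustment on offer depends on a test of baseline balance and uses a model for binary outcomes. It can serve the primary endpoint, but not a score that the next paragraph declares continuous. As written, the plan has no workable adjustment for these scales. What is at stake is precision, and an adjustment decision that depends on the data.

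Second, GOSE is ordered by the article's own description but is classed as continuous. On the t-test route, the step from death to vegetative state counts the same as the step between two grades of good recovery. On the Mann–Whitney route the comparison is sound, but the planned summary is a median and interquartile range, with no estimate of the shift across the scale. A judgement about normality, made on the outcome data, decides which route is taken.

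**Working it through.** **The plan's own figure.** There is none to reproduce. The power statement under Sample size justification concerns the primary endpoint only. From that section I take only the group size, 190 per arm.

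**1. Gain from the enrolment score (GCS, GMS, FOUR, CRS-R, DRS).**

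Inputs: 190 per arm (Sample size justification); two-sided 0.05 (Statistical analysis); correlation r between enrolment and follow-up score, which the article does not give and which is assumed to be 0.3 to 0.6.

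Reference effect, chosen so that the unadjusted comparison has 80% power (my reference point, not a claim of the plan):

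(1.960 + 0.842) × √(2/190) = 0.287 SD

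Linear adjustment multiplies the residual variance by 1 − r². Power becomes Φ(2.802/√(1 − r²) − 1.960), and the equivalent unadjusted total is 380/(1 − r²).

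| r (assumed) | Residual variance × | Variance cut | Power | Equivalent unadjusted total |
|---|---|---|---|---|
| 0 (no adjustment) | 1.00 | 0% | 80.0% | 380 |
| 0.3 | 0.91 | 9% | 83.6% | 418 |
| 0.4 | 0.84 | 16% | 86.4% | 452 |
| 0.5 | 0.75 | 25% | 89.9% | 507 |
| 0.6 | 0.64 | 36% | 93.8% | 594 |

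Below the assumed range, at r = 0.2, the cut is 4% and power is 81.6%. The variance factor does not depend on the group size. The power column assumes that all 190 per arm have a score.

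**2. Does the conditional correction already supply this?** Three features say not. It is triggered by a detected imbalance, whereas the gain in step 1 arises whether or not the arms are balanced. Its named examples are age and the admission GCS, not the enrolment value of each scale. Its model is logistic, which needs a categorical outcome.

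**3. What classing GOSE as continuous costs.** An illustration with assumed inputs: control proportions of 15, 20, 20, 12, 10, 8, 8 and 7% from death upwards; common odds ratio 1.7; 190 per arm; deaths kept as the lowest category; 3,000 simulated trials.

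- t test: 83.4% power
- Mann–Whitney: 83.7% power

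The simulation error of each figure is about √(0.834 × 0.166/3000) = 0.7 percentage points, so the two cannot be told apart. The loss is in the effect estimate and in pre-specification, not in power.

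**The case against.** The best defence is that nothing here is invalid. Unadjusted comparisons of randomised groups are unbiased, and only secondary endpoints are involved. That stands, and it limits the point to efficiency and clarity.

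For GOSE, an eight-category scale is unlikely to be judged normal. The Mann–Whitney test would then probably be used, and it is valid for ordered data. This also stands, and step 3 supports it. What remains is that the choice is left to a look at the outcome data and that no ordinal effect measure is named.

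The correlations are assumed, and they could be low. Entry requires a GCS of 4–8 or GMS below 5 on admission, which may narrow the enrolment scores too. That is why the range starts at 0.3 and r = 0.2 is also shown.

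The five scales are themselves bounded sums of graded items, so a linear model for them is an approximation. That is fair. It is the approximation the article already accepts on its t-test route, and a rank-based companion analysis can cover it.

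A reader might go further and infer that patients who died are lost from the scale comparisons, leaving survivors only. The article does not say so. It includes all randomised patients, records deaths and has a GOSE category for death. It gives no value for death on the other scales (of the DRS, for instance, it says only "Scores range from 0 to 29, with higher values indicating greater disability"). That silence is not an exclusion, and the predetermined analysis plan mentioned under Data management may settle it.

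A reader might also infer 24 separate tests (3 scales × 3 visits + 3 scales × 5 visits). Since only two-group tests are named, that is a natural reading, but the article does not state it.

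**Conclusion.** The point holds for efficiency and pre-specification, not for validity. For GCS, GMS, FOUR, CRS-R and DRS, the stated analysis leaves collected enrolment scores unused. At assumed correlations of 0.3 to 0.6 this forgoes a 9% to 36% cut in residual variance, worth about 10% to 56% more patients on those endpoints (1/0.91 = 1.10; 1/0.64 = 1.56). These sizes rest wholly on the assumed correlations and on roughly linear relations. On the Mann–Whitney route they are only indicative.

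For GOSE, calling the scale continuous conflicts with the article's own description of it. The consequence is a missing ordinal effect estimate and a choice of summary that depends on the data. The cost in power is negligible in the one scenario examined.

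It would be too strong to say that precision is lost on every scale: GOSE has no enrolment value to adjust for. Nor do the documents support a claim of survivor bias. The primary endpoint is not affected. The change is worth making before the database is locked, but the trial does not depend on it.

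**What to change.** In the Statistical analysis section, or in the analysis plan before database lock:

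- **GCS, GMS, FOUR, CRS-R, DRS.** State that the groups are compared with the enrolment value of the same scale and centre (the stratification factor) as pre-specified covariates, regardless of any imbalance test. Use ANCOVA, or one repeated-measures model per scale with the 6-month contrast as the main result. Limit the conditional logistic correction to outcomes it fits, or remove it.
- **GOSE.** State that it is analysed as an ordinal outcome with death as the lowest category, by a proportional-odds model adjusted for age and enrolment GCS, reporting the common odds ratio. Keep the Mann–Whitney test as a companion that does not rely on the proportional-odds model. No normality judgement is then needed.
- **Deaths on the other five scales.** Say in one sentence how they are handled, or point to where the analysis plan does so. This is a clarification only.

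Cost: wording only, as every variable is already collected. GMS is missing from one of the two enrolment lists, so confirm that it is recorded. The downsides are slightly more complex models to report and a proportional-odds assumption to examine.

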## Discussion

Right median nerve electrical stimulation has been adopted as a safe, inexpensive, non-invasive therapy for the neuroresuscitation of coma patients for more than two decades. There are several advantages to stimulating the right median nerve instead of other parts of body. First, the right median nerve is a peripheral portal to the central nervous system, and the sensory representation of the hand in the cortex is disproportionately large compared to other parts of the body. Second, Broca’s motor/speech planning area is in the left frontotemporal region in most individuals. Several possible mechanisms may underlie the effects of this treatment.

The first is that the spinoreticular component of the median nerve pathway synapses with neurons of the ascending reticular activating system (ARAS) [14]. The ARAS is a complex neural network connecting the reticular formation of the brain stem to the cerebral cortex via excitatory relays in the intralaminar nuclei of the thalamus. Therefore, the ARAS plays an important role in maintaining a state of wakefulness [26–29]. Studies have shown that the ARAS is activated by RMNS applied with a painful intensity [30], which may be a pathway for the therapeutic function of electrical stimulation.

A second mechanism is related to neurotrophins such as nerve growth factor and brain-derived neurotrophic factor (BDNF). Neurotrophic factors, which play an important role in neuroplasticity, may promote synaptic remodelling and changes in receptor expression or activation [31]. Previous studies have found that BDNF might enhance the survival of neurons after a hypoglycaemic coma [32]. Studies have also shown that BDNF levels increase in environmental enrichment animals compared to those housed in standard conditions [33]. RMNS, serving as a type of environmental enrichment, may raise the concentration of neurotrophins, leading to the survival of more neurons and hastening the recovery of comatose patients.

Increases in cerebral blood flow may be another pathway through which RMNS functions. In a research project conducted by Liu and colleagues, six comatose patients underwent SPECT scans for cerebral perfusion evaluation before and after the stimulation, and brain perfusion was found to have increased in all cases [20]. Other mechanisms include RMNS-induced changes in neurotransmitters such as dopamine and glutamate [34, 35] and improved electroencephalogram activity [16].

Over the years, a great number of researchers have focused on this treatment. However, because of the limitations of the studies mentioned above, its efficacy in accelerating recovery and improving overall outcomes has not been well established. Our ACES trial addresses right median nerve electrical stimulation therapy applied at an early phase (7–14 days post injury), with a standard stimulation protocol continuing for 14 days and with follow-up for 6 months.

This trial has some novel features compared with other major RMNS trials. First, it is an Asian multicentre randomised controlled trial. The previous trials only focused on one region or even a single hospital. This trial is the first to widen the scope to a whole continent, reducing selection bias to a great extent. Second, in this trial, the RMNS therapy starts at an early stage, 7–14 days after the injury. Research shows that the later the application of electrical stimulation, the longer the duration needed to obtain a similar outcome [14]. Earlier commencement of neuroresuscitation treatment can show more efficacy, as long as the patient is stable. Third, the ACES trial uses various kinds of assessment scales to evaluate the condition of participants. The assessments fall into two groups: recovery pace parameters and long-term outcome parameters. The former group includes the GCS, GMS and FOUR. The GCS includes eye opening, verbal and motor responses. It has been used ubiquitously in acute care databases and in studies of acute neurologic injury. However, the GCS has been deficient in measuring key components of neurologic examination used for prognostication and most conspicuously lacks assessment of the brainstem reflexes. The FOUR score has been developed to overcome these inadequacies. It consists of four components that evaluate eye responses, motor responses, brainstem reflexes and respiration patterns. Because of its greater neurologic detail, the FOUR score is of more benefit than the GCS in predicting mortality in the ICU. A recent large multicentre prospective study in critically ill patients found an excellent inter-rater agreement between paired clinicians [36–38]. The long-term outcome parameters are the CRS-R, DRS and GOSE. The CRS-R is a standardised neurobehavioural assessment tool comprising six hierarchically organised subscales (auditory, visual, motor, oromotor–verbal, communication and arousal). Scores range from 0 to 23, with higher scores indicating a higher level of neurobehavioural function [1]. The DRS, a measure of functional outcome, includes measures of eye opening, verbalisation and motor response; cognitive understanding of feeding, dressing and grooming; degree of assistance and supervision required; and employability. Scores range from 0 to 29, with higher values indicating greater disability [1, 39]. The GOSE has eight ordered categories: death, vegetative state, lower severe disability, upper severe disability, lower moderate disability, upper moderate disability, lower good recovery and upper good recovery. It was developed as an extended version of the GOS in response to the perceived lack of sensitivity of the latter. It is now the primary outcome measure in trials of TBI [40]. Using all these scales, we hope to evaluate the condition of the coma patients as thoroughly as possible.

TBI-related coma remains an important topic for today’s neuroscientists owing to its high incidence, poor outcomes and the heavy burden it places on families and society. RMNS therapy is promising. It is hoped that the ACES trial will provide valuable information regarding the question: Is right median nerve electrical stimulation able to facilitate a faster awakening and a better long-term outcome in TBI comatose patients? and lead to optimal use of median nerve electrical treatment.

## Trial status

The study is currently recruiting participants.

## Abbreviations

BDNF: Brain-derived neurotrophic factor
CRF: Case report form
CRS-R: Coma Recovery Scale-Revised
CS: Conscious state
DRS: Disability Rating Scale
FAM: Functional Assessment Measure
FIM: Functional Independence Measure
FOUR: Full Outline of Unresponsiveness (scale)
GCS: Glasgow Coma Scale
GMS: Glasgow Coma Scale Motor Part
GOS: Glasgow Outcome Scale
GOSE: Extended Glasgow Outcome Scale
MCS: Minimally conscious state
RMNS: Right median nerve stimulation
TBI: Traumatic brain injury
VS: Vegetative state
